## Abstract

**Background:**

Acute illness is the most common presentation of children to ambulatory care. In contrast, serious infections are rare and often present at an early stage. To avoid complications or death, early recognition and adequate referral are essential. In a recent large study children were included prospectively to construct a symptom-based decision tree with a sensitivity and negative predictive value of nearly 100%. To reduce the number of false positives, point-of-care tests might be useful, providing an immediate result at bedside. The most probable candidate is C-reactive protein, as well as a pulse oximetry.

**Methods:**

This is a diagnostic accuracy study of signs, symptoms and point-of-care tests for serious infections. Acutely ill children presenting to a family physician or paediatrician will be included consecutively in Flanders, Belgium. Children testing positive on the decision tree will get a point-of-care C-reactive protein test. Children testing negative will randomly either receive a point-of-care C-reactive protein test or usual care. The outcome of interest is hospital admission more than 24 hours with a serious infection within 10 days. Aiming to include over 6500 children, we will report the diagnostic accuracy of the decision tree (+/− the point-of-care C-reactive protein test or pulse oximetry) in sensitivity, specificity, positive and negative likelihood ratios, and positive and negative predictive values. New diagnostic algorithms will be constructed through classification and regression tree and multiple logistic regression analysis.

**Discussion:**

We aim to improve detection of serious infections, and present a practical tool for diagnostic triage of acutely ill children in primary care. We also aim to reduce the number of investigations and admissions in children with non-serious infections.

**Trial Registration:**

ClinicalTrials.gov Identifier: NCT02024282

## Background

Acute illness is the most common reason for encounter of children attending ambulatory care.

In a primary care setting, less than 1% of children assessed will have a serious illness [1]. The incidence of serious infections in children is assumed to be 5 to 10 times higher at the paediatric emergency department [2]. Febrile illness accounts for 20% of all paediatric ED visits [3].

Serious infections are rare in children in developed countries, but associated with considerable morbidity and mortality [4]. In Flanders, infectious diseases are responsible for 8.0% of all deaths in children under the age of one year, and for 13.6% of deaths in children aged 1 to 14 years [1, 5]. These numbers are comparable to death rates previously reported in the UK [6]. Serious infections in children are usually defined as sepsis, meningitis, pneumonia, pyelonephritis, gastroenteritis with dehydration, osteomyelitis, complicated abscess, viral respiratory infection with hypoxia, and cellulitis [7]. The mortality of meningococcal disease can be as high as 25% [8]. Besides this, approximately 7% of children who survive bacterial meningitis suffer from hearing loss [9].

Serious infections need to be distinguished from the vast majority of self-limiting viral conditions in children. Those few children with a serious infection can present at an early stage when the severity of the infection is not yet apparent [4]. At that point, their symptoms tend to mimic those of children with a non-serious illness. The rapid deterioration could cause a diagnosis to be missed at first contact, sometimes with severe consequences. Early recognition and adequate referral of serious infections are of vital importance to avoid complications. A faster and more accurate recognition of serious diseases could prevent unnecessary investigations, referrals, treatments and hospitalisations in children without serious illness, avoiding traumatic experiences for the child, parental concerns and health care expenditures.

### Assessment of serious infections

Clinicians use signs and symptoms to assess the probability of a serious infection and to decide on further management. To investigate the predictive value of these signs and symptoms, Van den Bruel et al. conducted a trial, which prospectively included almost 4000 children, resulting in a decision tree based on signs and symptoms [10]. This tree had a sensitivity and negative predictive value of nearly 100%. The risk of having a serious infection in children testing positive and thus indicating referral for further testing, however, was approximately 10%. If applied in clinical practice without caution, this decision tree could cause far too many children to be referred to hospital.

Vital signs are uncommonly measured in children in general practice [11]. If measurement of vital signs would become part of routine care, they could be useful in detecting serious infections in acutely ill children [12, 13]. A pulse oximetry, alongside other vital signs measurements has shown to differentiate children with serious infections from those with self-limiting infections in paediatric emergency care [13]. Validation of these results in low prevalence settings might aid clinicians to measure vital signs objectively.

A systematic review of the literature in all relevant databases identified the laboratory tests used to detect serious infections in febrile children in ambulatory settings [14, 15]. The most probable candidates for this purpose are CRP and procalcitonin (PCT). CRP can predict bacterial aetiology of community-acquired pneumonia [16]. PCT correlates with severity of urinary tract infections and sepsis and of community-acquired pneumonia in children [17, 18]. Despite these promising results, evidence is not yet conclusive and other tests may be valuable as well, urging for a large-scale trial.

POC tests are defined as laboratory and other services provided to patients at bedside. The physician has an immediate result and management can be adjusted accordingly. This makes them especially attractive in situations where a fast decision is warranted, such as urgent-access ambulatory care. They are minimally invasive, and thus relevant in paediatric care.

In diagnostic tests and clinical prediction rules a sensitivity of 100% is hard to achieve, because patients present at different stages in the evolution of their illness. At an early stage classic “red flag” features of serious illnesses tend to be absent. Safety netting is an integral part of the diagnostic process to deal with this situation. Neighbour and Almond et al. defined safety netting and sought clinical consensus about what safety netting should include: (I) the existence of uncertainty and how to communicate this to the patient or parent, (II) what exactly to look out for, (III) guidance on how exactly to seek further help and (IV) what to expect about time course [19–21]. Safety netting strategies and subsequent action should be evaluated on their effect on patient outcome, referral rate, antibiotic prescribing, and parental anxiety. In the ERNIE 2 trial, we will provide formal safety netting to a random sample of all children with a negative result on the decision tree, as described by Lemiengre et al. [22]. This includes a parent leaflet with instructions on how to detect and treat certain symptoms (e.g. fever), or a deterioration of the child’s condition, as well as when and how to re-consult the physician.

In this study, we aim to validate this decision tree in a new population and explore the added value of technological tests, such as Point-of-Care (POC) tests in diagnosing serious infection in acutely ill children in ambulatory care.

This trial is part of the ERNIE2-trial, which also comprehends a cluster randomised controlled trial to evaluate the effect of a POC CRP test and a brief intervention combined with a written safety net advice on additional testing, re-consultation and the antibiotic prescribing rate in acutely ill children not suspected of serious disease in primary care, as described by Lemiengre et al. [22].

## Methods

### Design

This is a prospective diagnostic accuracy study in ambulatory care (defined as general practice, paediatric outpatient clinics or emergency departments) identifying the diagnostic value of signs, symptoms and technological tests in diagnosing serious infections using hospital admission more than 24 hours for a serious infection as the main outcome measure (Figure 1).

**Figure 1 Fig1:**
[figure not shown]
**Study design.** POC CRP, point-of-care C-reactive protein; m, month; y, year.

### Participants

Children aged 1 month to 16 years, presenting to a family physician or paediatrician in Flanders, Belgium, with a new acute illness episode of maximum 5 days will be included consecutively. Children will be excluded if the acute illness is caused by merely traumatic or neurological conditions, intoxication, psychiatric or behavioural problem, or an exacerbation of a known chronic condition. If a physician includes the same child twice within 5 days, we will consider the second registration as a repeated measure and discard it subsequently from the analysis. Physicians will be instructed to recruit children consecutively during the inclusion period. If a physician includes less than five children over the study period, the assumption of consecutive inclusion is probably violated, and his or her results will subsequently be excluded from the analysis.

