### Outcome measures

#### Primary outcome measure

Serious infections, defined as a hospital admission for more than 24 hours for any of these diagnoses:Sepsis (including bacteraemia) with a pathogenic bacteria isolated from a haemoculture as the reference standardMeningitis (viral or bacterial) with a positive lumbar puncture (pleocytosis in cerebrospinal fluid and identification of a bacteria or a virus) as the reference standardAbscess with a positive culture as the reference standardPneumonia (viral or bacterial) with an infiltrate seen on chest x-ray as the reference standardOsteomyelitis (pathogens from bone aspirate as the reference standard, or if unavailable with a MRI or bone scan suggestive for osteomyelitis)Cellulitis (acute suppurative inflammation of the subcutaneous tissues)Gastro-enteritis with dehydrationComplicated urinary tract infection (positive urine culture (>10^5^/ml pathogens of a single species) and systemic effects such as fever)Viral respiratory tract infections complicated by hypoxia (e.g. bronchiolitis)

If a serious infection occurs within 10 days after inclusion, it will be considered a consequence of the same illness episode. To ensure a firm definition of the outcome (a serious infection), the outcome will be measured through three strategies: (I) a thorough search of each child’s electronic medical record at the hospitals within the referral region of the participating FP or paediatrician, (II) the results from interviewing the physician who included the child in the study, and finally (III) the results from the diary filled out by parents after consulting the FP, mentioning the date the child is no longer ill.

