### Sample size

Based on the binomial distribution, at an expected sensitivity of 97% with a minimal acceptable lower confidence limit of 85%, the minimal number of cases is 59, not taking into account the non-monotonic nature of power as a function of sample size due to discreteness of the binomial distribution [24]. The number of controls, derived through the formula N_controls_ = N_cases_ [(1-Prevalence)/Prevalence], [25] is 7316 at a prevalence of 0.8% and 6497 at a prevalence of 0.9%.

Considering the sample size calculation, we aimed to include 6500 children (in 88 general practices and 12 paediatric units), across Flanders, in urban and rural areas over a period of 12 months.

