### Implementation

#### Recruitment of physicians

We will compose a letter with a short description of the research and the (dis)advantages of participating, with the option to request further information. This letter will be distributed by email to all FPs known to the research partners trough personal and professional contacts. Interested family physicians (FPs) will be contacted and visited by the researchers to inform them more extensively about the trial. Participating FPs will complete a short questionnaire about practice characteristics. For more details about this questionnaire, we refer to Lemiengre et al. [22]. After agreement to participate, all physicians will be visited and instructed on the inclusion process. At this point in time, we will inform the FPs about their allocation by the investigator. The step-by-step plan will be explained in detail. All FPs will get a demonstration to properly perform the POC CRP test.

We will ask the paediatricians involved in the project steering committee and their colleagues affiliated with a university hospital to participate in the study and include eligible children at the outpatient clinic, as well as the emergency department. We’ll ask them to contact other interested colleagues affiliated with hospitals across Flanders, with a workload of acutely ill children similar or higher compared to the university hospitals. After agreement to participate, a meeting with all participating paediatricians will be organised to explain the trial in detail. All paediatricians will get a demonstration to perform the POC CRP test.

Parents will be informed through posters in the waiting room, as well as flyers, with a short comprehensible description of the background, aims and requirements to participate. Physicians will inform every eligible child and their parent(s), delivering an information leaflet and asking formally to participate. Parents and children from the age of 12 will sign a written informed consent form, with a permission to access the hospital medical record in case of a possible admission. We will provide adjusted information leaflets and consent forms for minors below and above 12 years of age.

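### The repeat-registration rule stops at one physician, so a child included first by a family physician and then by a participating paediatric unit can count as two cases from one infection

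*Protocol article*

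**What the plan says.** The repeat rule stands under Methods, Participants: "If a physician includes the same child twice within 5 days, we will consider the second registration as a repeated measure and discard it". Eligibility in the same section is limited to children "with a new acute illness episode of maximum 5 days will be included consecutively".

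The outcome (Primary outcome measure) is "Serious infections, defined as a hospital admission for more than 24 hours for any of these diagnoses". Its time window is: "If a serious infection occurs within 10 days after inclusion, it will be considered a consequence of the same illness episode". One of the three ways of finding outcomes is "a thorough search of each child’s electronic medical record at the hospitals within the referral region of the participating FP or paediatrician".

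The Design section takes ambulatory care to be "defined as general practice, paediatric outpatient clinics or emergency departments". Under Recruitment of physicians, paediatricians are asked to "include eligible children at the outpatient clinic, as well as the emergency department", alongside the family physicians. Under Participants, all physicians are told to recruit consecutively.

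The Sample size section plans on sensitivity: "at an expected sensitivity of 97% with a minimal acceptable lower confidence limit of 85%, the minimal number of cases is 59". It aims for 6500 children from 88 general practices and 12 paediatric units. Nothing in the article links or removes registrations of one child made by different physicians.

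**The concern.** The study recruits at points that one sick child may pass through in turn. A family physician who suspects serious illness refers the child, and the receiving clinic or emergency department may itself be recruiting. The repeat rule does not reach that second registration, because a different physician makes it. Both rows then look forward 10 days and find the same admission.

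Three things follow for the sensitivity estimate.

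- **Duplication depends on the outcome.** Children seen again at hospital level are enriched for serious infection, so the extra rows fall mainly among the cases, where there are few.
- **The rows are not independent.** A binomial interval treats two rows from one child as two cases and is too narrow.
- **The second score comes later in the illness.** The Background says that early presentations tend to lack clear signs. A child missed by the family physician may score positive at the second contact, and the pooled figure then shows one miss and one hit where there was one missed case. A rule meant for triage in primary care should not have its misses diluted in this way.

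The case count has no slack either, so duplicates could make the planned number appear to have been reached.

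**Working it through.** **1. The plan's own figures.** Controls = cases × (1 − P)/P. At P = 0.8%: 59 × 0.992/0.008 = 7316. At P = 0.9%: 59 × 0.991/0.009 = 6496.6, i.e. 6497. Both agree with the article. For the 59 cases the article gives neither the confidence level nor the probability of success. An exact (Clopper-Pearson) search at true sensitivity 97% gives 59 as the first sample size if one assumes a one-sided 95% limit of at least 85% reached with 95% probability. Success then means at least 55 of 59 detected, with probability 0.968.

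**2. Following the rules for one child.** A family physician includes the child on illness day 1. A participating emergency department includes the child on illness day 2. The child is admitted for more than 24 hours with pneumonia.

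- Eligibility: both contacts are within 5 days of illness, so both qualify.
- Repeat rule: two physicians, so as written it does not apply.
- Outcome: the admission lies within 10 days of both inclusions.

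Result: two case rows from one infection.

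**3. The same physician on days 6 to 10.** The child was already ill at the first inclusion. Six or more days later the same illness has lasted more than 5 days and is not eligible. This route stays open only if the second contact is judged a new episode.

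**4. Slack in the case count.** 6500 × 0.008 = 52 and 6500 × 0.009 = 58.5 expected cases, against 59 needed. If 2, 5, 10 or 20% of 59 case rows were duplicates (assumed), there would be 58, 56, 53 or 47 distinct cases. The success probability in step 1 would be 0.904, 0.913, 0.926 or 0.833, against 0.968. It does not fall smoothly because the binomial is discrete, as the article itself notes.

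**5. Effect on the lower limit.** Assume that k of 59 case rows are second registrations, all tree-positive, with two rows missed. The distinct children detected are (57 − k)/(59 − k). The two-sided 95% lower limit is the 0.025 quantile of Beta(x, n − x + 1), with x detected of n.

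| Assumed duplicates k | Detected | Sensitivity | Lower limit | Shift from 88.3% (points, before rounding) |
|---|---|---|---|---|
| 0 | 57/59 | 96.6% | 88.3% | – |
| 1 | 56/58 | 96.6% | 88.1% | 0.2 |
| 2 | 55/57 | 96.5% | 87.9% | 0.4 |
| 3 | 54/56 | 96.4% | 87.7% | 0.6 |
| 8 | 49/51 | 96.1% | 86.5% | 1.7 |
| 10 | 47/49 | 95.9% | 86.0% | 2.3 |

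(Subtracting the rounded limits gives 1.8 for k = 8.) Every limit stays above 85%.

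**6. A lower true sensitivity.** With 46 of 51 distinct cases detected, sensitivity is 90.2% and the lower limit 78.6%. Adding 8 tree-positive duplicates gives 54/59 = 91.5% and 81.3%. The estimate rises by 1.3 points and the limit by about 2.7. Both limits are below 85%.

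**The case against.** The case on the other side is substantial.

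- **The 5-day and 10-day windows serve different purposes.** One removes repeat index measurements and the other attributes outcomes, so their lengths need not match. A reader might infer that the mismatch alone lets one physician routinely count an admission twice. The article does not support that: the 5-day illness limit closes nearly all of that route (step 3). This part of the objection stands.
- **The outcome is narrow.** A reader might take any admission within 10 days to count. Only admissions of more than 24 hours for a listed infection do.
- **A second registration is not automatic.** The receiving unit must participate, its physician must recruit the child, and consent must be obtained. The frequency is unknown, and 8 to 10 duplicates among 59 is an assumption at the high end.
- **A miss is not erased.** The family physician's false negative stays in the data, so it is diluted rather than replaced. That every duplicate is tree-positive is also assumed.
- **The wording could be generic.** The rule might be meant for any physician. The text does not say so, and the next rule in the same section, on physicians with fewer than five inclusions, plainly means one individual.
- **Linkage is data handling, often left to a fuller document.** That would answer an omission. Here a rule is stated, and following it as written keeps the second physician's record.

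The cross-physician gap survives all of these.

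**Conclusion.** The rule as written allows one serious infection to enter the sensitivity estimate as two cases when different physicians include the same child. This follows from the text and needs no assumption about numbers. The size does: it depends on an unknown duplicate count, on the duplicates being tree-positive, and on an exact two-sided 95% interval. On that basis the lower limit is overstated by a few tenths of a point if duplicates are rare and by about 2 points if they are common.

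A reader might infer that duplicates would overturn the study's conclusion on sensitivity. The scenarios do not show that: in none does removing the duplicates move the lower limit across 85%. The harm is to the independence of the case rows, the width of the interval, and the visibility of misses in general practice. Severity is moderate.

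**What to change.** Define the repeat rule by child and illness episode instead of by physician. For example: registrations of the same child by any participating physician, in any setting, within the 10-day outcome window are linked as one episode; the first is the index record in every pooled estimate, and later ones serve only as follow-up information. Where accuracy is reported separately by setting, a child may appear once in each setting. Count the planned 59 cases as distinct episodes and report how many registrations were linked.

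The cost is record linkage across sites and slightly fewer rows. Since the hospital-record search already has to identify each child, the extra work should be modest. Using 10 days also settles the remaining case of a second contact judged a new episode. The price is that a truly separate illness starting within those 10 days is treated as follow-up, which is consistent with how the article already attributes outcomes.

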### Index tests

#### 5-stage decision tree

As part of a thorough history taking and physical examination, we will ask physicians to score the 5-stage decision tree, as developed by Van den Bruel et al. [10].

Children testing positive on this tree will always get a POC CRP test.

Children testing negative on this tree presenting to primary care will either get a POC CRP test, or usual care, depending on their per practice cluster randomisation, as described by Lemiengre et al. [22].

#### POC CRP test (finger stick)

We searched the literature in multiple databases and performed a survey of manufacturers, completed with personal contacts in order to identify tests that would be marketed shortly for acute infections in children in primary care. For use in children, important criteria of a feasible test are the sample volume (<5 μl) and the test duration (<5 minutes). Two point-of-care CRP tests (Afinion CRP test on the Afinion AS100 Analyzer, Alere, USA and CRP test on the LifeAssays™ Reader by LifeAssays, Sweden) met our criteria.

A pilot study was performed to determine the user-friendliness of these POC CRP devices. Only the Afinion CRP test on the Afinion AS100 Analyzer met our standards for user-friendliness. It is a user-friendly device, especially because a small drop of blood is enough to perform the test, what makes it perfect for use in children, and only two simple operations are needed to get the result (aspirating blood in the capillary, putting the cassette in the machine). In this pilot study, the analytical accuracy of the selected POC CRP device was also examined, demonstrating an agreement between the CRP test results on the Afinion AS100 Analyzer and the Cobas c702 (Roche Diagnostics, Switzerland) with a mean difference of 0.1% (95% CI: −17.6% to 17.4%) and perfect correlation (y = 1.01×-0.04) even at high CRP concentrations [23].

The Afinion™ CRP Test Cartridge consist of a 1.5 μL glass capillary to be filled with blood from a finger stick and a reagent container. First, the sample is automatically diluted with a liquid that also lyses the blood cells. Then, the sample mixture is aspirated through the membrane coated with anti-CRP antibodies, and all CRP in the sample is concentrated on this membrane. The conjugate solution containing anti-CRP antibodies labelled with ultra-small gold particles is then sucked through the membrane. The gold-antibody conjugate binds to the immobilized CRP on the membrane, which will turn red-brown. Excess gold-antibody conjugate is removed by a washing solution. The analyser measures the colour intensity of the membrane, which is proportional to the amount of CRP in the sample. The result is available within 4 minutes. The CRP measuring range is 5–150 mg/L.

We will instruct all physicians to properly perform the POC CRP test. For internal quality control, a low and a high control positive will be measured at regular intervals to confirm the efficacy and correct performance of the test according to the manufacturer’s instructions. The device distributor will provide technical assistance.

